### Sample size calculation and statistical analysis

The sample size was based on previous trials [7, 9, 10], assuming that SRI mean score was about 50 in usual NIPPV care after 1 year of treatment. We defined a non-inferiority margin of 5 for the difference in SRI mean score between the two groups, as the difference was found in previous researches about the effect of NIPPV with oxygen therapy vs oxygen therapy alone [9, 10]. On the assumption of a Standard Deviation (SD) of 20 [27] and a loss to follow-up of 25%, a sample size of 100 participants per group was needed to detect a difference of at least 5 between groups with a one-sided alpha of 0.025 and a beta of 0.1.

Continuous variables will be presented as mean and SD for normally distributed data or median and interquartile range (IQR) for nonnormally distributed data. Categorical variables will be presented as absolute numbers and percentages. Differences in continuous variables between two groups will be tested with the Student *t* tests or Mann–Whitney *U* test as appropriate.

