The categorical variables will be compared by chi-square tests or Fisher’s exact tests as appropriate. We will use a general linear repeated measures analysis of variance with a Bonferroni correction or a paired t-test to analyze assessments changes within a group over time. The primary and appropriate secondary outcome analyses, such as compliance with the ventilator, change in arterial PaCO2 and lung function, will be performed including all randomized patients according to the intention-to-treat (ITT) principle. Missing data will be handled using the “last observation carried forward” method. We will use a linear mixed model to analyze the mean difference between the groups. When the conditions for use of the linear mixed model are not appropriate, a generalized estimating equation with correction for the baseline value and minimization variables (age, body mass index, frequency of COPD readmissions over 12 months) will be used. Time from randomization to death will be performed according to the ITT principle using the Kaplan–Meier approach and the log rank test. Hazard rate will be analyzed using a Cox proportional hazards regression model adjusted for minimization covariance. When the conditions for use of are not appropriate, the time-dependent cox regression model will be used. Safety analyses will be performed on all randomized patients. Additionally, per-protocol analyses of all outcomes will be analyzed as a sensitivity analysis, including patients finishing the study according to the protocol.

Two-sided P values less than 0.05 will be considered to be statistically significant. Statistical analyses will be performed using SPSS software (version 25.0, IBM SPSS).

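### The primary SRI comparison can switch from a mixed model with no stated covariates to a covariate-adjusted GEE on an undefined trigger, so two different primary tests are available

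*Protocol article*

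**What the plan says.** All of this stands in the protocol article under Sample size calculation and statistical analysis, unless noted.

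- First-choice model: "We will use a linear mixed model to analyze the mean difference between the groups". No covariates are listed for it.
- Fallback: "When the conditions for use of the linear mixed model are not appropriate, a generalized estimating equation with correction for the baseline value". No diagnostic, threshold, time point or decision-maker is given for the move from one model to the other.
- Other covariates, attached to the fallback only: "minimization variables (age, body mass index, frequency of COPD readmissions over 12 months) will be used".
- Analysis set and missing data: the primary analysis "will be performed including all randomized patients according to the intention-to-treat (ITT) principle", and "Missing data will be handled using the “last observation carried forward” method". The LOCF sentence comes directly before the mixed-model sentence.
- Error rate: "Two-sided P values less than 0.05 will be considered to be statistically significant". The sample size uses a one-sided 0.025.
- Blinding: Randomization and masking says that the statistical analysts do not know the assignment. The limitations paragraph of the Discussion says the data analyses are done blinded.
- Table 1 schedules the SRI at allocation and at 3, 6 and 12 months, so a baseline SRI is available for every analysis.

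**The concern.** A conditional estimator for the primary outcome is harmless only if the condition is fixed in advance and judged without sight of the treatment comparison. Here the condition is left open, and whether a mixed model's assumptions are met can be judged only on the outcome data. The two branches differ in more than estimation technique. Correction for baseline SRI, age, body mass index and readmissions is attached to the GEE alone, so the switch also changes the covariate set. An unadjusted and a baseline-adjusted estimate of the same difference can lie well apart in a single trial, and one can be significant when the other is not.

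Two things are at stake. The stated 5% error rate holds for one fixed model, not for a choice between two. And if the mixed model is used without baseline SRI, the primary comparison loses precision that the trial has already paid for.

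The fallback covariates raise a further problem. The readmission count is not dated relative to randomization, while hospitalization frequency during the trial is a secondary outcome. Read as the on-study count, it would adjust the primary result for something the intervention may change. The covariates are also called minimization variables, although Randomization and masking describes only a computer-generated random sequence.

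**Working it through.** The plan gives no figure for this point beyond its 5% significance level, so there is nothing to reproduce first. The check asks what that level becomes if either model may be reported.

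**Inputs.** From the protocol article: two-sided 0.05; SD 20; 100 per group; 25% loss, hence 100 × 0.75 = 75 evaluable per arm. Assumed, because the article does not give it: correlation ρ between baseline and 12-month SRI of 0.5 to 0.8. Also assumed: the mixed model is unadjusted, the data are complete, and the covariates other than baseline SRI carry no prognostic information.

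**Step 1: precision.** Adjusting for baseline multiplies the variance of the 12-month difference by 1 − ρ². The reduction is ρ²: 0.5² = 25%, 0.7² = 49%, 0.8² = 64%. With 75 per arm, the unadjusted standard error is 20 × √(2/75) = 3.27 points. Adjusted, it is 3.27 × √(1 − ρ²): 2.83 at ρ = 0.5, 2.33 at 0.7 and 1.96 at 0.8.

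**Step 2: how different the two tests are.** Under the null, the unadjusted and baseline-adjusted estimates correlate at r = √(1 − ρ²).

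**Step 3: chance that at least one rejects.** This is 1 − P(|Z₁| < 1.96 and |Z₂| < 1.96), with Z₁ and Z₂ bivariate normal with correlation r.

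| ρ | r | At least one rejects |
|---|---|---|
| 0.5 | 0.87 | 7.3% |
| 0.7 | 0.71 | 8.3% |
| 0.8 | 0.60 | 8.8% |

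Two independent tests would give 1 − 0.95² = 9.75%, so the inflation is less than that of a full second test. On the one-sided 0.025 scale of the sample size, the figures are about half: 3.7 to 4.4%.

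**Step 4: simulation.** With 100 per arm, visits at baseline and 3, 6 and 12 months, complete data, and 3,000 trials per setting, a random-intercept mixed model or adjusted GEE used alone rejects in 4.5 to 5.7%. At least one of the unadjusted mixed model and the adjusted GEE rejects in 8.1% (ρ = 0.5), 8.7% (0.7) and 8.3% (0.8). A separate simulation with 75 per arm, ρ = 0.65 and 20,000 trials gives 5.2% for each test and 8.8% for either.

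**Step 5: does fixing the model remove dropout bias?** Simulation at ρ = 0.7 with no true difference, dropout of about 32 to 37% in one arm and 22% in the other, related to the last score only in the first (the dropout mechanism is an assumption). After LOCF, the bias at 12 months is:

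- unadjusted mixed model: +1.2 to +1.7 points
- adjusted mixed model: +1.2 to +1.8 points
- GEE: +1.2 to +1.8 points

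The adjusted mixed model and the GEE give identical estimates on the LOCF-completed data. The bias comes from LOCF, so settling the model leaves it in place.

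**The case against.** The strongest reply is that the text is a conditional rule with a named fallback and named covariates, not permission to report whichever P value is smaller. The 7 to 9% supposes that the choice is made on the result every time, and blinded analysts cannot know which arm a choice favours. The mixed model may also carry the same covariates. In that case the two estimates nearly coincide, and the two tests differ mainly in their standard errors. The criterion and the covariates may be set out in a full protocol or SAP not shown here.

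Much of this stands, and it is why the figure is a ceiling. It does not remove the point. Blinding to arm does not hide P values: with coded arms, an analyst still sees which model falls below 0.05. The article does not merely omit a detail. It states a data-dependent switch and ties the covariates to one branch only.

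A reader might infer something stronger: that, with outcome-related dropout, the switch trades a valid estimator for a biased one. The document does not support that. LOCF is specified, so the mixed model has no missing-at-random protection left to lose, and step 5 shows the same bias in both models. Even on observed data, the bias of GEE needs conditions that the article does not state. In simulation, GEE with independence working correlation was off by −1.6 to −2.0 points when score-related dropout differed by arm. GEE with exchangeable correlation was off by 0.2 at most. With equal score-dependence in both arms, every model was within 0.1. Nor is the mixed model on observed data assured validity: the withdrawal rule counts death, intubation and serious adverse events, so missing at random is itself an assumption.

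**Conclusion.** The point holds as a matter of pre-specification. The primary SRI model depends on an undefined judgement, and the switch as written changes both the estimator and the covariates. If the mixed model is unadjusted, the worst-case two-sided error is about 7 to 9% instead of 5%. This rests on an assumed correlation of 0.5 to 0.8 and on selection by result, which the blinding statements restrain but do not exclude. The actual inflation lies somewhere between none and that ceiling. On the same reading, leaving out baseline SRI forgoes 25 to 64% of variance reduction, and that loss does not depend on how anyone behaves.

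No claim is made that GEE is an invalid method or that the fallback introduces dropout bias. This deserves correction before the analysis, but it does not undermine the design by itself.

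**What to change.** Name one primary model: a mixed model for repeated measures on SRI at 3, 6 and 12 months, with baseline SRI as a covariate and robust (sandwich) standard errors whatever the residuals look like. State the 12-month contrast and any further covariates in advance. Delete the sentence that allows the switch, and keep GEE only as a labelled sensitivity analysis with the same covariates. If a readmission count is kept as a covariate, define it as the count before randomization.

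Analyse observed data rather than LOCF-completed data in this model. Otherwise the dropout bias in step 5 remains whichever model is chosen.

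The cost is a wording change. Baseline SRI and all three visits are already in the assessment schedule, so no new data are needed. The only statistical downside is slightly wider intervals if the robust errors exceed the model-based ones.

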**Methods:**

This multicenter, prospective, randomized controlled trial was conducted with a total of 200 COPD patients with chronic hypercapnic respiratory failure. Using a computer-generated randomization process, patients were randomized (in a 1:1 ratio) into the usual NIPPV (control group) or to receive additional IOT-based management (intervention group) for 12 months. The primary outcome was the Severe Respiratory Insufficiency (SRI) questionnaire. Secondary outcomes included compliance with the ventilator, gas exchange, lung function, health-related quality of life, hospitalization frequency, time to death within 1-year, all-cause mortality, safety analysis, and cost-effectiveness analysis.

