### Randomization and masking

The randomization of the trial was completed at an independent data center (College of Public Health, Fudan University) using a computer-generated random number sequence with an allocation ratio of 1:1 for each group. All investigators at each of the participating hospitals contacted an independent statistician to obtain an identification code and a random number unique to this patient who fulfills the inclusion criteria. IOT-based management of NIPPV couldn’t be blinded, and an effective sham measure was not available. Supervising clinicians who performed NIPPV and IOT-based management were aware of the treatment assignment of every participant. The staff members conducting the outcome assessments and statistical analysts were blinded to treatment assignment.

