This study protocol has limitations which must be addressed. First, blinding of investigators was not possible due to IOT-based management of NIPPV, and it could induce bias. Nevertheless, the staff members conducting the outcome assessments would be blinded to the intervention. Moreover, all data analyses would be performed in a blinded fashion. Second, between-physicians differences in the experience of NIPPV management might affect the results of this study. IOT cloud platform would provide available information and enhance communication between patients, physicians, nurse practitioners and ventilator providers. However, the integrated care managements did not represent a criterion, but provided a personalized care. Third, appropriate adjustment of NIPPV treatment need home visit or hospitalization. Remotely adjusting of ventilator parameters was not available and needs more research. Fourth, several confounding factors associated with general therapy for stable COPD, such as pharmacologic therapy and pulmonary rehabilitation, were only suggested and not protocolized. The general therapy was to be performed in accordance with routine clinical care and pharmacologic therapy was recorded at each follow-up.

In conclusion, this study will be the first and largest randomized trial done in China to evaluate the effectiveness and safety of the IOT-based management of NIPPV for COPD patients with chronic respiratory failure. The results will improve home NIPPV treatment and management in the future.

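### The protocol describes a 1:1 random sequence but analyses by minimisation variables, and for the SRI score it writes baseline and factor adjustment only into the fallback model

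*Protocol article*

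**What the plan says.** On allocation, the abstract's Methods paragraph says: "Using a computer-generated randomization process, patients were randomized (in a 1:1 ratio". Randomization and masking says the independent data centre did this "using a computer-generated random number sequence with an allocation ratio of 1:1 for each group", and that investigators "contacted an independent statistician to obtain an identification code and a random number unique to this patient". Neither place mentions minimisation, stratification or any balancing factor.

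On analysis, Sample size calculation and statistical analysis introduces the main between-group model with one sentence: "We will use a linear mixed model to analyze the mean difference between the groups". No covariates follow. If that model's conditions are not met, the plan moves to "a generalized estimating equation with correction for the baseline value and minimization variables (age, body mass index, frequency of COPD readmissions over 12 months". For the hazard of death it plans a "Cox proportional hazards regression model adjusted for minimization covariance".

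Table 1 schedules the SRI score at allocation (Day 1) and at 3, 6 and 12 months. The sample-size paragraph rests on the SRI mean after one year: "We defined a non-inferiority margin of 5 for the difference in SRI mean score between the two groups". It assumes an SD of 20, 25% loss to follow-up, one-sided alpha 0.025 and beta 0.1, and arrives at 100 per group.

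**The concern.** Minimisation assigns each patient in the light of the covariates of those already enrolled. A random number sequence with no named factors does not. The analysis section takes the first for granted and the randomisation section describes the second. This matters beyond labelling, because the allocation method decides which standard error is correct for an analysis that leaves the factors out.

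The second problem is where the adjustment sits. For the SRI score, the baseline value and the three factors are attached to the fallback and not to the main model. Read as printed, a change of estimation method made after seeing the data would also change the covariates, so two things move at once. Baseline SRI is measured in every patient and is probably the strongest available predictor of 12-month SRI, so leaving it out of the main model would waste precision that costs nothing to obtain.

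**Working it through.** 1. **Allocation, side by side.** The abstract and Randomization and masking give a computer-generated 1:1 sequence with a number issued per patient and no factors. The analysis section names age, body mass index and COPD readmission frequency as minimisation variables and uses the minimisation factors again in the Cox model. Nothing in the article links the two accounts.

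2. **The plan's own sample size.** Per group, n = 2 × (1.960 + 1.282)² × 20² / 5² = 336.2, so 337 evaluable. Allowing for 25% loss, 337 / 0.75 = 449.3, so 450 randomised. The stated 100 per group is not reproduced. That is a separate defect, but it sets the background: 100 per group less 25% leaves 75 evaluable.

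3. **Unadjusted precision at 75 per group.** SE = 20 × √(2/75) = 3.27. Power to exclude a margin of 5 with a true difference of 0 and one-sided alpha 0.025 is Φ(5/3.27 − 1.96) = 33%.

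4. **Adding baseline SRI.** The SE is multiplied by √(1 − ρ²), where ρ is the correlation between baseline and 12-month SRI. The documents do not give ρ, so 0.3 to 0.8 is an assumed range.

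| ρ (assumed) | Residual SD | SE | SE reduction | Power, 75 per group |
|---|---|---|---|---|
| 0 | 20.0 | 3.27 | – | 33% |
| 0.3 | 19.1 | 3.12 | 5% | 36% |
| 0.5 | 17.3 | 2.83 | 13% | 42% |
| 0.7 | 14.3 | 2.33 | 29% | 57% |
| 0.8 | 12.0 | 1.96 | 40% | 72% |

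Reaching 90% power with 75 per group would need ρ = √(1 − 75/336.2) = 0.88.

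5. **Omitting the factors if allocation was minimised.** This was simulated with 8,000 runs, 150 patients, three binary factors, a biased-coin probability of 0.8, SD 20, no true effect and a two-sided 5% test. The share of SRI variance explained by the factors (R²) is also an assumption.

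| R² (assumed) | Mean model SE, factors omitted | True SD of the estimate | SE overstated by | Type I error, omitted | Type I error, adjusted |
|---|---|---|---|---|---|
| 0.10 | 3.26 | 3.10 | 5% | 3.8% | 5.0% |
| 0.25 | 3.26 | 2.84 | 15% | 2.4% | 5.0% |
| 0.40 | 3.27 | 2.57 | 27% | 1.4% | 5.0% |

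Under unminimised 1:1 allocation in the same simulation, the unadjusted test stays at about 5% (4.9% to 5.4%).

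**The case against.** The strongest reply is that the article is condensed. It gives the mixed model one sentence and never says that model is unadjusted; the covariates may be in the full protocol or analysis plan. A mixed model that takes Day 1 SRI as a repeated response would already recover most of the baseline information. This stands, and it is why the precision loss is stated as possible and not as certain. It does not remove the point, because the article does list covariates and attaches them to the fallback.

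It can also be said that the randomisation section never calls the sequence unrestricted, and that contacting a statistician for each patient is compatible with minimisation. That is fair. The text does not show which account is wrong, only that they do not agree as printed.

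The planned analysis is intention-to-treat with last observation carried forward, so the nominal set is 100 per group. Unadjusted power is then 42%, rising to between 46% and 84% over the same range of ρ. The relative gain in SE is unchanged.

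A reader might infer more than the documents support:

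- That the factors appear nowhere but in the fallback. The Cox model uses them too, so the mismatch concerns the SRI analysis.
- That the test is anti-conservative. Any error in the SE arises only if minimisation was used, and then it makes the SE too large.
- That the mixed model targets an average over visits and dilutes a late effect. The wording is the ordinary phrase for a difference in means, and the documents give no trajectory. The article simply does not tie the model to a visit.
- That centre must be a model term. The Discussion's remark that "between-physicians differences in the experience of NIPPV management might affect the results of this study" concerns clinicians' experience; adding centre would be a preference.

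**Conclusion.** The point holds in two parts. First, the sections on randomisation and on analysis disagree about whether allocation was minimised. This follows from the text and needs no assumption. Second, for the SRI score the stated adjustment belongs to the fallback and not to the main model, so the choice of model also changes the covariates, and baseline information may go unused.

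The size of the second part depends on figures outside the documents. Over ρ from 0.3 to 0.8 the possible gain is a 5% to 40% smaller SE. If minimisation was used, leaving its factors out overstates the SE by about 5% to 27% for R² from 0.10 to 0.40. Both are losses of power, with no inflation of false positives. Adjustment is worth having but does not by itself close the gap between 75 and 337 evaluable per group.

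**What to change.** - State in Randomization and masking the allocation method actually used. If it was minimisation, name the factors and the random element there; if not, drop the minimisation label from the analysis section and call the variables prognostic covariates.
- Pre-specify the primary mixed model with baseline SRI, either as a covariate or with Day 1 SRI as a response whose mean is constrained equal across groups, together with age, body mass index and prior COPD readmissions.
- Define the readmission count as before randomisation. The present wording gives only a 12-month span, follow-up is also 12 months, and hospitalisation frequency is a secondary outcome.
- Use the same covariate set in the GEE, so that a change of model changes only the estimation method.
- Name the 12-month difference in SRI as the primary contrast, to match the one-year basis of the sample size.

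The cost is wording in the protocol and analysis plan, settled before unblinded data are analysed. Baseline SRI is already scheduled. The baseline list and Table 1 do not name body mass index or prior-year readmissions explicitly, so confirm that both are on the case report form.

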**Fig. 3 Fig3:**
[figure not shown]
The study flow diagram. NIPPV, noninvasive positive pressure ventilation; COPD, chronic obstructive pulmonary disease; IOT, Internet of things; CHRF, chronic hypercapnic respiratory failure

The enrolled patients who are lost to follow-up, suffered serious adverse events, withdraw consent, or met endpoints will be regarded as a withdrawal. The Intervention and follow-up was terminated If one of the endpoints occurs: (1) death; (2) did not receive intervention as randomized; (3) the need for endotracheal intubation and invasive ventilation during exacerbation; (4) pneumothorax; (5) had active unstable coronary artery syndrome or cerebrovascular disease; (6) unable to tolerate noninvasive ventilation due to surgery and so on; and (7) cognitive impairment or unstable psychiatric morbidity.

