### Outcome and assessments

The primary study outcome was the SRI questionnaire, a 49-item questionnaire specifically designed for chronic respiratory failure patients with home mechanical ventilation. The domain scores are calculated by transforming the mean item score into a percentage ranging from 0 (worst quality of life) to 100 (best quality of life) [29, 30]. SRI questionnaire could not be an outcome but the score of SRI questionnaire.

Secondary outcomes were compliance with the ventilator, change in arterial PaCO2 and PaO2, change in lung function, time to readmission or death within 12 months from any cause, all-cause mortality, exacerbation and hospitalization frequency, safety analysis, cost-effectiveness analysis, and other health-related quality of life, measured by the modified Medical Research Council score (MRC) [31] to assess dyspnea (0 = no dyspnea, 4 = dyspnea at rest), the COPD assessment test (CAT) [32, 33], and COPD nocturnal symptom assessment test (cNAT).

Adherence with the ventilator was observed by monitoring the daily usage, usage days, ventilator settings, and other parameters in the IOT platform. Arterial blood gas analysis was taken during the daytime at rest without oxygen or ventilatory support unless patients were unable to stop ventilatory support even for short periods. Lung function was assessed according to national guidelines [28], including FEV1, FEV1% predicted, FVC, FVC % predicted, FEV1/FVC, total lung capacity, and residual volume. Hospital readmission and survival status of study patients were collected by checking medical records from the hospital or the general practitioner at each follow-up visit. For patients lost to clinical follow-up, each study center collected data from the national population register.

Occurrence time, severity, duration, adopted measure, and outcome of the adverse event occurring during the study should be recorded in the adverse events form according to the actual circumstances (Additional file 2). The common adverse events included facial rash, nasal ulceration, dry eyes, conjunctivitis, nasal stuffiness, nosebleed, gastric distension and device/mask intolerance [11, 17]. Serious adverse events were life-threatening, result in death, persistent, and significant disability, or incapacity, or make the participants’ hospitalization.

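### The per-protocol set holds only finishers yet is applied to every outcome, so it contains no deaths in either arm and its SRI and PaCO2 comparisons are selected on completing 12 months

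*Protocol article*

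**What the plan says.** All references are to the protocol article.

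- **Per-protocol set** (Sample size calculation and statistical analysis): "per-protocol analyses of all outcomes will be analyzed as a sensitivity analysis, including patients finishing the study according to the protocol". Membership depends on finishing, and no outcome is exempted.
- **Withdrawal** (Follow-up and endpoints, text after Fig. 3): enrolled patients who are "lost to follow-up, suffered serious adverse events, withdraw consent, or met endpoints will be regarded as a withdrawal". The next sentence says that intervention and "follow-up was terminated If one of the endpoints occurs: (1) death", followed by six further events.
- **Serious adverse events** (Outcome and assessments): "Serious adverse events were life-threatening, result in death, persistent, and significant disability, or incapacity, or make the participants", with hospitalisation completing the list.
- **Outcomes** (same section): "The primary study outcome was the SRI questionnaire". The secondary outcomes include "time to readmission or death within 12 months from any cause, all-cause mortality, exacerbation and hospitalization frequency", and change in PaCO2.
- **Main analysis**: the primary and appropriate secondary analyses "will be performed including all randomized patients according to the intention-to-treat (ITT) principle". Time to death is also by intention to treat, and safety uses all randomised patients.
- **Non-inferiority**: the sample size section sets a margin of 5 SRI points. The Background also names non-inferiority as an aim for PaCO2, mortality and readmission.

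**The concern.** A per-protocol set should select on eligibility and on whether patients received what they were allocated. This one selects on reaching the end of the study, and death is one of the events that stops a patient reaching it. The set therefore selects on an outcome that it is meant to analyse.

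Two things are at stake. First, the planned check on mortality cannot agree or disagree with the main result. Second, for SRI and PaCO2 the check compares only patients who completed 12 months. Where a non-inferiority margin is stated, the per-protocol result is normally read beside the intention-to-treat result, so readers will give this analysis more weight than an ordinary sensitivity analysis.

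**Working it through.** The plan gives no figure for the size or event count of the per-protocol set, so there is none to reproduce. The check follows the definitions, with one numerical illustration.

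**Step 1: deaths.** The set is the finishers. A patient who dies has met endpoint (1), follow-up has ended, and the patient is a withdrawal. So the set and the patients who died do not overlap, and per-protocol deaths are 0 in each arm. Example with assumed rates: 12-month mortality of 10% and 20% with 100 patients per arm is 100 × 0.10 = 10 and 100 × 0.20 = 20 deaths by intention to treat. The per-protocol table shows 0 and 0. With no events, the log-rank statistic has observed and expected counts of 0, and the Cox partial likelihood is the same for every hazard ratio. There is no estimate.

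**Step 2: time to readmission or death.** Every death drops out of this composite. So does any readmission of a patient who later died, because that patient is not a finisher.

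**Step 3: SRI.** Assumptions: SRI mean 50 and SD 20 (the planning values), the same underlying SRI distribution in both arms, and a correlation of 0.5 between SRI and a latent survival score. The mortality rates and the correlation are not in the document. If the fraction m with the lowest latent score dies, the survivors' mean is

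50 + 20 × 0.5 × φ(z_m)/(1 − m),

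where φ is the standard normal density and z_m the m-quantile.

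| m | φ(z_m) | Survivors' mean SRI |
|---|---|---|
| 0.30 | 0.348 | 50 + 10 × 0.348/0.70 = 54.97 |
| 0.20 | 0.280 | 50 + 10 × 0.280/0.80 = 53.50 |
| 0.10 | 0.175 | 50 + 10 × 0.175/0.90 = 51.95 |

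Intervention minus control:
- control 30%, intervention 20%: 53.50 − 54.97 ≈ −1.5
- control 30%, intervention 10%: 51.95 − 54.97 ≈ −3.0
- control 20%, intervention 30%: 54.97 − 53.50 ≈ +1.5

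A simulation of the same model gave −1.48, −3.00 and +1.42. The shift runs against the arm with fewer deaths and is 30% to 60% of the margin (1.5/5 and 3.0/5). PaCO2 is exposed to the same selection. The document gives no inputs from which to size it.

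**Step 4: readmissions.** Two sets of statements point in opposite directions.

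- *Readmitted patients leave the set*: any serious adverse event is a withdrawal, and hospitalisation is a serious adverse event.
- *Readmitted patients stay*: hospitalisation is not among the seven numbered events that end follow-up. Table 1 and Outcome and assessments collect readmission at each visit. Hospitalisation frequency is an outcome, and the main economic endpoint relates cost to admissions avoided. Follow-up and endpoints also has all patients admitted to hospital for their scheduled visits, so a fully literal reading could make every attending patient a withdrawal.

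The second set makes it unlikely that the literal reading was intended, but the text does not settle the matter.

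**The case against.** The strongest reply is that nothing important rests on this analysis. The primary outcome and time to death are analysed by intention to treat, safety uses all randomised patients, and population-register data are collected for patients lost to clinical follow-up. A mortality table of zeros would be noticed at once. This stands, and it confines the harm to the sensitivity analysis. It does not remove the harm, because the plan commits to a per-protocol analysis of every outcome and states a non-inferiority margin.

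A second reply is that an analysis plan would define the set. Adherence thresholds and deviation lists can indeed be left to it. But the article does not leave membership or scope open. It states both, and together they give an empty mortality analysis.

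A third is that SRI cannot be measured after death in any set. That is true, but the intention-to-treat analysis keeps earlier values from patients who die, by carrying the last observation forward. The finishers-only set discards these patients altogether.

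A reader might also infer three stronger points that the document does not support:
- **That per-protocol readmissions are zero by construction.** This needs the literal joining of two definitions that other parts of the article contradict (step 4).
- **That the selection favours a finding of no difference.** In the illustration it creates a difference where none exists, and the sign changes with which arm has more deaths.
- **That the set has at most 200 × (1 − 0.25) = 150 patients.** The 25% is a planning assumption about loss to follow-up, not a ceiling, and loss to follow-up is only one of the withdrawal categories.

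**Conclusion.** The point holds for death on the text alone, with no outside assumption. Per-protocol mortality is 0 in both arms whatever the truth, its hazard ratio cannot be estimated, and time to readmission or death loses all its deaths. Per-protocol SRI and PaCO2 are conditioned on completing 12 months, a post-randomisation outcome. The bias can be material against the margin of 5, but its size rests on the assumed mortality and correlation in step 3, and its direction depends on differential mortality and withdrawal. For readmission, the finding is an unreconciled conflict between passages, not a proven zero. The main analyses are unaffected. The definition should be corrected before the data are analysed.

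**What to change.** 1. Define the per-protocol set by eligibility and receipt of the allocated management without major deviation, up to the patient's event or last contact, not by completing 12 months.
2. Keep patients who die, are readmitted or have a serious adverse event in the set, with their data to that point.
3. Limit the per-protocol analysis to SRI and PaCO2, and analyse death and readmission by intention to treat.
4. Reconcile the withdrawal wording, the serious-adverse-event definition and the collection of readmissions to 12 months, so that it is clear who counts as a withdrawal for analysis. This concerns analysis sets only. When treatment should stop is a clinical matter for the investigators.

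The cost is small: rewording the per-protocol definition and, for analysis purposes, the withdrawal sentence. No new data are needed.
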